## Abstract

**Background:**

Incomplete or delayed implementation of Guidelines can lead to potentially avoidable medication-related harm. All Australian residential aged care facilities (RACFs) are recommended to have access to a multidisciplinary medication advisory committee (MAC) to provide clinical governance of medication management. The objective of this trial is to evaluate the effectiveness and relative net benefit of using knowledge brokers, supported by a national quality improvement collaborative, to implement Australia’s new Guiding Principles for Medication Management in Residential Aged Care Facilities (Guiding Principles).

**Methods:**

The Maximising Embedded Pharmacists in AGed CAre Medication Advisory Committees (MEGA-MAC) trial will be conducted in partnership with RACFs operated by three aged care provider organizations across four states of Australia. The intervention will involve knowledge broker dyads (pharmacist plus a MAC representative [e.g. nurse]) developing, implementing and evaluating RACF-specific local action plans to implement the Guiding Principles in up to 15 RACFs. Knowledge broker dyads will be supported by a national quality improvement collaborative (MEGA-MAC collaborative) comprising clinical experts, implementation scientists and resident and caregiver representatives. An interrupted time series design will be used to assess change over time with three pre-intervention (-6, -3 and 0 months) and three post-intervention assessment time points (+ 3, + 6, + 9 months). The primary outcome will be change in pre/post RACF-level concordance with the Guiding Principles measured using quality indicators (score 0 to 28, higher scores = greater concordance). A net benefit analysis will be conducted to examine the relative costs and benefits of implementing the intervention.

**Discussion:**

The MEGA-MAC trial investigates a novel multifactorial knowledge translation strategy to improve the uptake of guidelines and support safe and appropriate use of medication in RACFs. We anticipate that the findings will provide new information on the role of healthcare professionals as knowledge brokers, MACs, and quality improvement collaboratives for effective guideline implementation in RACFs.

**Ethics and dissemination:**

Ethics approval obtained from Monash University and Grampians Health Human Research Ethics Committees. Findings will be disseminated through professional and lay media, conference presentations and peer-reviewed publications.

**Trial registration:**

Australian New Zealand Clinical Trial Registry (ANZCTR): ACTRN12624000894594. Registered 22nd July 2024 – Prospectively registered. https://www.anzctr.org.au/ACTRN12624000894594.aspx

**Supplementary Information:**

The online version contains supplementary material available at 10.1186/s13012-025-01449-0.

Contributions to Literature• This trial is the first to evaluate the use of knowledge broker dyads and a quality improvement collaborative to improve concordance with guidelines in residential aged care facilities• This trial is the first to evaluate the net-benefit of a knowledge broker intervention in residential aged care facilities.• This trial will evaluate novel system-level roles for pharmacists and medication-advisory committee representatives.• If effective, the knowledge translation strategy could be adapted to other therapeutic areas and settings, and evaluated to determine its effect on the safety and effectiveness of medications for older adults.

## Background

Medication safety in older people remains a global public health challenge. The World Health Organization (WHO) has recognized the importance of medication safety through its Medication without Harm Global Patient Safety Challenge [1]. However, poor implementation of clinical guidelines and evidence-based guideline recommendations remains a key barrier. The 2024 WHO Global Research Agenda on Knowledge Translation and Evidence-informed Policy Making identifies the need to improve efficiencies and synergies of knowledge translation in healthcare [2], and the WHO identifies governance and leadership as key factors required to strengthen residential care systems [1, 3].

In Australia, people living in residential care are prescribed an average of 10 regular medications, and over half are prescribed potentially inappropriate medications, which may result in adverse events or unplanned hospitalizations [4, 5]. There is up to fourfold variability across residential aged care facilities (RACFs) in nine of the 10 most prevalent medications, with this variation unlikely to be explained by clinical characteristics of residents alone [6]. This highlights the potential value of knowledge sharing and benchmarking across RACFs. In 2021 the Australian Commission on Safety and Quality in Health Care identified 10 priority action areas for residential aged care, including a need to improve the governance, composition and operation of Medication Advisory Committees (MACs) (priority 4) and a recommendation to trial the role and impact of onsite aged care pharmacists (priority 10) [7].

A MAC is a “multidisciplinary committee that provides overarching governance of medication management within a RACF to ensure the judicious, appropriate, safe and quality use of medicines” [8]. All RACFs in Australia are required to establish or have direct access to a MAC. Australian MACs share similarities with international quality circles (multidisciplinary peer review groups) that support primary healthcare professionals [9, 10]. as well as hospital-based drug and therapeutics committees [11]. Our previous work highlighted the importance of multidisciplinary MAC membership, scope for greater pharmacist involvement, and the need to leverage data (e.g. quality indicators) to inform quality improvement and practice [12]. It also identified that MACs often work in isolation and opportunities exist to share learnings, experiences and insights to promote best practice [12]. This work informed the User Guide: Role of a Medication Advisory Committee (User Guide) published in 2022 by the Australian Government’s Department of Health and Aged Care [8]. However, a national survey of MACs conducted in 2023–24 revealed there is considerable variability in the structure and function of MACs, 58% of MACs reported their membership was multidisciplinary (medical, nursing and pharmacy) and 28% of MACs reported that they performed all recommended functions related to quality improvement [13].

In November 2022, Australian Government’s Department of Health and Aged Care published updated Guiding Principles for Medication Management in Residential Aged Care Facilities (Guiding Principles) [14]. The Guiding Principles support RACFs to promote a systems approach to medication safety. In particular, the Guiding Principles recommend parameters and procedures for medication management within RACFs, with good clinical governance an important tool to support implementation and monitoring of these processes. Effective implementation of the Guiding Principles, including the User Guide, which is a supplementary resource to the Guiding Principles, requires a targeted knowledge translation strategy. There is emerging evidence on the role of knowledge brokers and quality improvement collaboratives in facilitating guideline implementation in practice [15, 16]. Knowledge brokers are individuals or groups that help to move knowledge from those who create the knowledge (e.g. guideline developers) to those that use the knowledge (e.g. health care professionals) [15]. A quality improvement collaborative is a structured, multi-site initiative where healthcare professionals work together, supported by experts and a shared framework, to implement best practices, improve clinical processes, and enhance patient outcomes [17]. Quality improvement collaboratives are a cost-effective way to develop knowledge, motivation and quality improvement capacity of individuals and health systems [18, 19]. An Australian study involving a national quality improvement collaborative for implementing Australia’s Clinical Practice Guidelines and Principles of Care for People Living with Dementia demonstrated 42.1% immediate increase in clinician self-reported adherence to the guideline recommendations [16, 20].

The objective of this trial is to evaluate the effectiveness and examine the relative net benefit of using knowledge brokers, supported by a national quality improvement collaborative, to implement the Guiding Principles.

## Methods

### Design

The Maximising Embedded pharmacists in aGed cAre Medication Advisory Committees (MEGA-MAC) trial will use an interrupted time series design to investigate the effect of knowledge broker dyads (pharmacist and MAC representative) supported by a national quality improvement collaborative (MEGA-MAC collaborative) to implement the Guiding Principles (Fig. 1). This design will involve retrospective (pre-intervention) and prospective (post-intervention) data collection. This design was selected because the quality improvement collaborative involves interventions being delivered concurrently making alternate designs involving randomisation (e.g. stepped-wedge) less feasible. Interrupted time series analyses are considered a strong quasi experimental design for evaluating quality improvement initiatives and uptake of clinical practice guidelines [21, 22].

**Fig. 1 Fig1:**
[figure not shown]
Overview of the MEGA-MAC intervention

The trial was designed in partnership with the three participating aged care provider organizations and the following foundational activities:Online survey of 120 current MACs in Australia to explore structure, scope and function of MACs [13]. The survey was based on the Department of Health and Aged Care Audit tool and checklist for a Medication Advisory Committee [23] and the User Guide: Role of a Medication Advisory Committee [8].Semi-structured interviews with 20 MAC members in Australia to explore the current structure, scope and function of MACs.Systematic review of the roles and effectiveness of knowledge brokers in implementing clinical practice guidelines [15].15 semi-structured interviews with early adopters of Australia’s embedded on-site aged care pharmacist model [24].Ongoing learnings from the Evidence-based Medication knowledge Brokers in Residential Aged CarE (EMBRACE) trial [25].

This trial protocol conforms to the Standard Protocol Items: Recommendations for Interventional Trials (SPIRIT) guidelines (Appendix 1) [26, 27]. The economic evaluation will be conducted alongside the trial and will be reported in accordance with the Consolidated Health Economics Evaluation Reporting Standards (CHEERS) checklist [28]. The trial was prospectively registered with the Australian and New Zealand Clinical Trials Registry (ANZCTR) [Registration #:ACTRN12624000894594. Date registered: 22/07/2024].

### Setting

The trial will involve up to 15 RACFs, and their MACs, operated by three aged care provider organisations in four Australian States (Victoria, New South Wales, South Australia, Western Australia). The three aged care provider organisations include one government and two not-for-profit organisations, and span across metropolitan, regional, rural and remote geographical regions. In Australia, RACFs provide care for individuals who’s care needs cannot be adequately met at home. Internationally, RACFs are often referred to as long-term care facilities or nursing homes [29, 30]. In Australian RACFs, medications are typically prescribed by visiting medical practitioners, dispensed by external community pharmacies, and administered by on-site nurses or credentialed aged care workers [31]. Some RACFs have their own MAC while other RACFs operate under the governance of an overarching MAC within a larger organisation. With an overarching MAC, the MAC should still identify, prioritise and address local medication-related issues at the individual RACF-level [8].

### Governance and engagement

The trial will be overseen by the Project Management Team comprising the lead investigators and Project Manager. The Project Management Team will meet with the aged care provider organisation representatives and knowledge broker dyads regularly throughout the study to monitor the data collection, conduct of the study and to identify and mitigate any potential risks.

The trial will be supported by a Project Interest Holder Group [32] comprising government agencies (Department of Health and Aged Care, Australian Commission on Safety and Quality in Health Care, Aged Care Quality and Safety Commission), professional groups (Australian and New Zealand Society for Geriatric Medicine, Royal Australian College of General Practitioners, Australian College of Nursing, Pharmaceutical Society of Australia, Pharmacy Guild of Australia), aged care provider organisations (Ageing Australia [formerly known as Aged and Community Care Providers Organisation]), primary health networks (Western Victoria Primary Health Network) and consumer and carer representatives (Older Persons Advocacy Network, Dementia Australia). The Project Interest Holder Group will meet every six months to provide overall strategic advice for the project, taking into consideration current and emerging practice issues. Additional meetings may be considered if needed. A Data Safety Monitoring Board will meet as and when required if potential or actual adverse events caused by the intervention are reported during the study. The Board will involve an independent group of three healthcare professionals with relevant clinical expertise (e.g. general practitioner, geriatrician, nurse, pharmacist).

### Recruitment, eligibility and consent of RACFs

The three aged care provider organisations’ leadership team will identify RACFs that are eligible and interested in participating. RACFs will be eligible if they have a MAC or commit to establishing a MAC by the commencement of the trial. Once eligible RACFs are identified at the aged care provider organisational level, a member of the Project Management Team will explain the trial to eligible RACFs, provide the explanatory statement and obtain written informed consent from the RACF manager or an authorised representative of the aged care provider organisation.

This will be a RACF-level intervention, individual residents will not be recruited to participate. Nurses, aged care workers, visiting pharmacists and medical practitioners at each RACF and MAC members will be made aware of the objectives of the trial and the nature of the intervention via letters, posters and notice boards. Residents and their families will be made aware of the trial through distribution of notices and posters at each RACF.

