### Data collection

Data will be collected from the participating RACFs at six timepoints (−6, −3, baseline, 3, 6, 9 months) by trained data collectors (aged care nurses, health or care professionals employed or contracted by each of the participating aged care provider organisations) (Table 2). Data collectors will attend an online training webinar on data collection led by the Project Management Team and will have access to data collection manuals and recorded training webinars to ensure consistency of data collection. Pre-intervention data (−6, −3, 0 months) will be collected retrospectively at or before baseline. Post-intervention data (+ 3, + 6, and + 9) will be collected prospectively. Trial data will be collected using a series of standard data collection forms and managed using Research Electronic Data Capture (REDCap), an electronic data capture tool hosted and managed by Helix (Monash University). REDCap is a secure, web-based software platform designed to support data capture for research studies [36, 37]. Trial data will be stored for a minimum of 15 years after publication of result in accordance with Australian National Health and Medical Research council (NHMRC) and Monash University guidance for medical research involving clinical trials. The final dataset will only be accessible to the investigators and statistician or epidemiologist.

**Table 2 Tab2:** SPIRIT diagram – schedule of enrolment, intervention and assessment for the MEGA-MAC study

	Study period							Data source
Timepoint (months)	Pre-intervention period		Enrolment	Baseline	Intervention period			
	−6	−3	*-t*	0	3	6	9	
RACF enrolment								
Eligibility screen			x					
Consent			x					
Intervention								
KB dyad recruitment			x					
MEGA-MAC collaborative panel recruitment			x					
KB training			x					
Intervention implementation				x	x	x	x	
Data collection								
RACF characteristics information				x				Clinical and administration records; knowledge broker dyads
MAC characteristics information				x			x	Clinical and administration records; knowledge broker dyads
KB dyad and MEGA-MAC collaborative panel demographic information			x					Knowledge brokers and MEGA-MAC members

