### RACF-level concordance with Guiding Principles

The data collectors will assess RACF-level concordance with the Guideline Principles using a series of indicators developed for the MEGA-MAC trial by New South Wales Therapeutic Advisory Group (NSW TAG), in consultation with an expert advisory group and the Project Management Team [38]. The indicators will assess concordance with the Guiding Principles across four key domains: the RACF’s 1) MAC meeting; 2) policies, procedures and guidelines; 3) admission processes; and, 4) medication review processes (Tables 3, 4, 5, and 6). There will be 28 indicators across the four domains.

**Table 3 Tab3:** Domain 1 Indicators and sub-indicators evaluating the RACF’s MAC meeting

Indicator	Numerator	Denominator	Target
Calculation of summary indicator			
Percentage of recommended medication governance activities undertaken by the RACF	Number of positive or NA responses to the listed RACF’s medication governance and management activities	9 (total number of responses)	High (towards 100%)
Sub-indicators regarding aspects of MAC structure or function		Possible responses	
1. The RACF’s MAC met in the last quarter		Yes/No	
2. The RACF’s MAC meeting was multidisciplinary		Yes/No	
3. When a MAC governs more than one RACF, a representative of this RACF was in attendance		Yes/No/NA*	
4. The RACF’s report of residents’ experiences from RACF residents, their carers, family and/or substitute decision-makers regarding medication-related issues was presented		Yes/No	
5. The RACF’s report of RACF storage of medicines was presented		Yes/No	
6. The RACF’s report of medication incidents was presented		Yes/No	
7. The RACF ‘s report of trends in the percentage (or numbers) of residents with polypharmacy was presented		Yes/No	
8. The RACF’s report of trends in the percentage (or numbers) of residents who received an antipsychotic medication was presented		Yes/No	
9. The RACF’s report of trends in the percentage (or numbers) of residents who received a comprehensive medication management review from an appropriately qualified pharmacist was presented		Yes/No	

^*^ NA is selected if the MAC governs one RACF only. One point is allocated for selecting N/A in response to this indicator

*MAC* medication advisory committee, *NA* not applicable, *RACF* residential aged care facility

**Table 4 Tab4:** Domain 2 Indicators and sub-indicators evaluating the RACF’s policies, procedures and guidelines

Indicator	Numerator	Denominator	Target

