## Outcomes

### Primary outcome

The primary outcome will be the change in RACF-level concordance with the Guiding Principles post-intervention compared to pre-intervention. Concordance with the Guiding Principles will be measured as a score out of 28. This score will be composed of 19 indicators measured dichotomously (no = 0, yes = 1) and 9 indicators measured continuously (proportion between 0 and 1) (Tables 3, 4, 5 and 6). Higher scores will indicate greater concordance with the Guiding Principles.

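### RACFs may enrol before they have a MAC, yet 9 of the 28 primary points score the MAC meeting, so meeting an entry condition can distort the period effect

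*Protocol article*

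**What the plan says.** The section on recruitment, eligibility and consent of RACFs sets this rule: "RACFs will be eligible if they have a MAC or commit to establishing a MAC by the commencement of the trial". Commencement is not tied to a month on the −6 to +9 timeline.

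The primary outcome section states: "The primary outcome will be the change in RACF-level concordance with the Guiding Principles post-intervention compared to pre-intervention". The score has 28 points: 9 in Domain 1 (MAC meeting, Table 3), 10 in Domain 2, 5 in Domain 3 and 4 in Domain 4. Domain 1 opens with "1. The RACF’s MAC met in the last quarter" and "2. The RACF’s MAC meeting was multidisciplinary". Its third item allows not applicable: "NA is selected if the MAC governs one RACF only. One point is allocated for selecting N/A in response to this indicator". That presupposes a MAC. Items 4 to 9 ask whether particular reports were presented. The article gives no scoring rule for a quarter in which no MAC existed.

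The data collection section adds: "Pre-intervention data (−6, −3, 0 months) will be collected retrospectively at or before baseline". The effectiveness analysis is a linear mixed model with a binary pre/post period, linear trial month, and site nested within MAC as random effects. A second model adds a period-by-month interaction. There is no control group. The MAC characteristics to be collected do not include a date of establishment or first meeting.

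**The concern.** The objective is the effect of knowledge broker dyads supported by a collaborative. Setting up a MAC is a condition of entry and is not among the listed dyad activities. A RACF that enrols on a commitment scores nothing on the MAC items while it has no MAC, then gains points once the MAC meets. That gain falls close to the start of the intervention.

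A random intercept cannot absorb a step within a site, and no concurrent control shows what would have happened without the brokers. Depending on when the new MAC first meets, the step can be counted as intervention effect or can appear as a false upward pre-trend that pulls the estimate down. The primary outcome and the Domain 1 secondary outcome are both exposed.

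**Working it through.** **Inputs from the protocol.** Assessments at −6, −3, 0, +3, +6 and +9 months; period = 0 up to month 0 and 1 afterwards; linear month term; up to 15 RACFs; Domain 1 = 9 of 28 points.

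**Inputs not stated (assumptions).** k = number of RACFs enrolled without a MAC. J = the step from the MAC simply existing and meeting, held constant once it starts: about 3 (items 1 to 3), at most 9. SD of the 28-point score: 2 to 5 points.

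**The plan's own figure.** The stated 86% power for 0.5 SD with 15 RACFs can be reproduced. Variance of the pre mean is (1 + 2×0.5)/3 = 0.667 and of the post mean (1 + 2×0.25)/3 = 0.5. Adjusting post for pre gives 0.5 − 0.25²/0.667 = 0.406, and Φ(0.5/√(0.406/15) − 1.96) = 0.86. This assumes a pre-post correlation of 0.25 and two-sided alpha of 0.05, neither of which is stated. It serves here only to fix the 0.5 SD target and to cost the fix.

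**Weights.** With complete data every site has the same six times, so random intercepts do not change the period estimate; it is the average of the site-level least-squares estimates. Regressing on intercept, period and month gives these weights on the six scores:

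0.417, −0.333, −1.083, 1.083, 0.333, −0.417

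**Share of J in each result, by when Domain 1 first scores.**

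| First scores at | Primary model, period | Primary model, slope per month | Interaction model, period at month 0 | Plain pre/post mean |
|---|---|---|---|---|
| +3 | 1.083 + 0.333 − 0.417 = 1.00J | 0 | 1.00J | 1.00J |
| 0 | 1.00 − 1.083 = −0.08J | 0.083J | 0.17J | 0.67J |
| −3 | −0.083 − 0.333 = −0.42J | 0.083J | −0.17J | 0.33J |

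The last column is for comparison only; a plain pre/post mean is not the primary analysis.

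**Effect on the trial mean.** Multiply by k/15.

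- First scores at +3: J×k/15. For J = 3 this is 0.2 points (k = 1) or 0.6 (k = 3). For J = 9 it is 0.6 or 1.8.
- First scores at 0: per affected RACF, −0.083×3/15 = −0.02 to −0.083×9/15 = −0.05.
- First scores at −3: per affected RACF, −0.417×3/15 = −0.08 to −0.417×9/15 = −0.25.

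**Against the design target.** If the SD is 2 to 5 points, 0.5 SD is 1.0 to 2.5 points. In the +3 case one affected RACF then supplies between 0.2/2.5 = 8% and 0.6/1.0 = 60% of the target.

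**The case against.** A reader might infer that the jump from no MAC to a MAC is simply scored as an effect of the knowledge brokers, and that a few such RACFs could supply most of the target effect. The documents do not support that.

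- **Timing.** The MAC must be in place by commencement. The dyad's MAC representative must be the chair or a current member, Table 2 places dyad recruitment before baseline, and Table 1 has the dyad training at −1 month. So a MAC probably exists before month 0. If it also meets in that quarter, Domain 1 first scores at month 0 and the primary model puts the step into the month trend. Full crediting needs a MAC that exists before month 0 but first meets afterwards. That is possible, since Table 1 has dyads presenting their plans at MAC meetings from month 0, but it is not established.
- **Size of the step.** Items 4 to 9 require specific reports, and getting these presented may well be the dyad's own work. The background section reports that 58% of surveyed MACs were multidisciplinary and 28% performed all recommended quality-improvement functions, so a new MAC would not score near 9 unaided; even item 2 is not automatic.
- **Number of sites.** The background section says: "All RACFs in Australia are required to establish or have direct access to a MAC". No count of RACFs without a MAC is given.
- **Safeguards.** The interaction model, the site and MAC predictions and the process evaluation might reveal an unusual site, and the statistical analysis plan, not shown, may hold sensitivity analyses.

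The first three points stand and limit the finding. The fourth stands only in part: nothing listed in the article corrects the primary estimate, and in the +3 case the interaction model gives the same 1.00J.

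**Conclusion.** The eligibility rule and the primary score do not fit together. The rule admits RACFs whose pre-intervention quarters may have had no MAC, while about a third of the score (9/28 = 32%) depends on MAC meetings. For such a RACF the primary period effect is shifted by 1.00J, −0.08J or −0.42J, according to a first-meeting date that the plan neither fixes nor lists for collection. Upward bias occurs only if the first scored meeting falls after month 0, and is then 0.2 to 0.6 points on the mean per affected RACF of 15. In the other two cases the bias is slight to moderate and downward.

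This rests on J between about 3 and 9 and on complete data. The number of affected RACFs and the score SD are not stated; if no RACF enrols on a commitment, there is no bias. Severity is moderate and conditional.

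**What to change.** 1. For RACFs not yet enrolled, replace the commitment clause with a requirement for a MAC, own or overarching, that was operating by the −6 month point.
2. If any RACF with a newly established MAC is enrolled, keep it in the intention-to-treat primary analysis and record the date of its MAC's first meeting.
3. Pre-specify two supporting analyses of the primary outcome: one excluding RACFs with a new MAC, and one on the 19 non-MAC points (Domains 2 to 4: 10 + 5 + 4) applied to all RACFs, so that scales are not mixed. Do not attribute the effect to the knowledge brokers unless these agree with the primary result.
4. State how Domain 1 is scored for a quarter with no MAC.

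Cost: a few sentences and one extra data field. One or a few RACFs may become ineligible, probably not many given the existing national requirement. The exclusion analysis loses some precision: under the power formula above, 86% with 15 RACFs becomes about 84% with 14 and 78% with 12. The 19-point analysis also drops any genuine Domain 1 gain, so compare its direction and its size per point, not its raw total. Settle this before outcomes are seen, because a later exclusion among at most 15 sites would look data-driven.
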